### Embedded process evaluation study

An embedded process evaluation study will run in parallel with the trial. The rapid feedback evaluation approach delivered by the Rapid Research Evaluation and Appraisal Lab at the Department of Targeted Intervention, University College London will combine qualitative data obtained from semistructured interviews with patients, carers and staff and documentary analysis (reports, meeting minutes, etc) to

Explore staff views and experiences with different approaches to recruitment.Examine patient and carer experiences in trial participation (understanding of trial literature, experience with treatment options and reasons for withdrawal).Examine patient and carer experiences of declining to take part in the trial.Identify barriers and enablers to trial set-up, recruitment and delivery from the point of view of staff.

Data obtained will be analysed and shared with researchers throughout the main ACCess study at a time when they can be used to inform within trial decision-making processes.^26^

### AE reporting

In accordance with the Research Governance Framework for Health and Community Care, any untoward medical occurrence in a trial participant will be considered an AE, recorded in the patient’s case notes and assessed for severity.^27^ Any AE that is life-threatening; results in death, birth defect or significant disability; or requires hospitalisation is considered an SAE. The following trial-specific AEs will also be considered SAEs:

A recognised perioperative complication of regional or local anaesthetic administration (including pneumothorax, inadvertent arterial puncture, inadvertent intraneural/intravascular injection, persistent neuropraxia and LA toxicity).The requirement for re-exploration or abandonment of surgery.

Full details including the nature of the event, start and stop dates, severity, actions taken, relationship to the trial specific intervention and outcome of all SAEs will be reported to the sponsor via the Glasgow Clinical Trials Unit on the eCRF and events will be followed up until satisfactory resolution. All SAEs will be assessed for causality and expectedness. Any SAE believed to be related to a trial-specific procedure that is thought to be unexpected (ie, the event is not listed within the protocol nor would not be expected to occur when carrying out the trial-specific procedure in normal clinical practice) will be considered a related unexpected serious adverse event (RUSAE) and must be reported to the sponsor within 24 hours of the site becoming aware. All SAEs will be reported to the IDMC, TSC and sponsor. The sponsor must inform the REC of any RUSAE within 15 days.

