#### Interventional arm: RA

An US-guided supraclavicular or axillary BPB will be administered by a consultant anaesthetist trained in RA or a trainee practising under direct supervision. The supraclavicular approach will be considered first-line, unless the anatomy or patient risk profile is unfavourable. In patients on antiplatelets or other anticoagulants, the choice between supraclavicular and axillary block will be at the anaesthetist’s discretion, taking into account ‘compressibility, vascularity and consequences of bleeding’.^18^ Where pulmonary disease is present, an axillary nerve block eliminates the risk of pneumothorax or temporary phrenic nerve paralysis.

A 1:1 mixture of 0.5% L-bupivacaine and 1% lidocaine, mixed with epinephrine to 1 in 400 000 final concentration, will be used (online supplemental appendix 1). Maximum dose limits are 2 mg/kg for bupivacaine and 7 mg/kg for lidocaine with epinephrine, recognising the effects are additive. The volume of LA injected must account for patient weight and maximum dose limits while considering the need for LA supplementation. In a study where the median patient weight was 66 kg, the ED_95_ (effective volume in 95% of patients) for supraclavicular blocks was 27 mL.^19^ A minimum volume of 25 mL must be injected for patients over 60 kg. This is reduced to 20 mL for patients weighing 51–60 kg and 15 mL in patients weighing <45 kg (online supplemental appendix 1). A suggested supraclavicular technique involves depositing a minimum of 25% of LA in the ‘corner pocket’ between the first rib and the subclavian artery and the remainder posterolateral to the plexus, avoiding deliberate intracluster injection.^20^ For axillary blocks, the same minimum volumes must be used, targeting 25% of the LA to the musculocutaneous nerve, with the remainder deposited around the ulnar, median and radial nerves, as well as the cutaneous nerves of the arm and forearm if visualised.

10.1136/bmjopen-2021-052188.supp1Supplementary data

Sensory and motor block of musculocutaneous, median, radial and ulnar nerves will be recorded every 5 min using a validated 3-point scale.^21^ Sensory blockade of the medial cutaneous nerve of the forearm and arm will also be recorded. Measurements will be continued until either sensory block is adequate or 30 min has elapsed, at which point the block may be supplemented by targeted US-guided axillary or midhumeral injection as appropriate.

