### Blinding

Due to the systemic effects of RA (motor blockade, visible venodilatation, etc), which do not occur with LA, it will not be possible to blind the patients, surgical or anaesthetic teams. Dialysis staff and staff performing follow-up visits will be blinded to the intervention. Ultrasound scan (USS) will also provide independent objective assessment of the AVF. The statisticians and health economist will be blinded to the intervention.

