### Statistical analysis plan

All statistical analyses will primarily be performed according to the intention-to-treat principle. However, additional analysis will be prespecified to address ‘failed blocks’ (eg, per-protocol, as treated, and complier-average causal effects analyses). Baseline demographics will be summarised by treatment group without formal statistical comparison. The primary outcome will be analysed using logistic regression, adjusting for stratification variables used at randomisation and the treatment group assigned. The treatment effect will be reported with a 95% CI for the OR and p value also reported. Time to loss of functional access will also be analysed using survival analysis regression methods. Similarly, for each of the secondary outcomes, analyses will be conducted using appropriate regression methods reporting the treatment effects, 95% CIs and p values. Safety data including the number of adverse events (AEs) and serious adverse events (SAEs) will be reported overall and by study arm, where no formal statistical testing will be carried out.

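### The SAE count by group mixes events defined by seriousness with events defined by attribution to the anaesthetic, so nerve deficits are open to unequal classification

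*Protocol article*

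**What the plan says.** The AE reporting section of the protocol article counts every untoward medical occurrence as an AE. It then sets general criteria for an SAE: "Any AE that is life-threatening; results in death, birth defect or significant disability; or requires hospitalisation is considered an SAE". These depend on consequences, not on cause.

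It goes on: "The following trial-specific AEs will also be considered SAEs". Two items follow. The first is "A recognised perioperative complication of regional or local anaesthetic administration", with examples "including pneumothorax, inadvertent arterial puncture, inadvertent intraneural/intravascular injection, persistent neuropraxia and LA toxicity". The second is "The requirement for re-exploration or abandonment of surgery".

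The Blinding section says that "it will not be possible to blind the patients, surgical or anaesthetic teams". Dialysis staff and the staff who carry out follow-up visits are blinded. The Statistical analysis plan section says that AE and SAE numbers "will be reported overall and by study arm, where no formal statistical testing will be carried out". The Outcomes section places the secondary outcome assessments, safety among them, at 3 and 12 months.

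**The concern.** The first trial-specific item differs from the general criteria in two ways. It needs no serious consequence: an inadvertent arterial puncture is listed with no requirement of harm. It also needs a judgement on cause, because neuropraxia enters only as a complication of giving the anaesthetic.

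The second feature matters most for nerve deficits. Both groups have a dissection at the wrist or elbow, so a lasting deficit in either group may have an uncertain origin. Someone who knows that a brachial plexus block was given may be readier to blame the block. Someone who knows that only local infiltration was given may be readier to blame the surgery. The first deficit becomes an SAE, while the second may stay an AE.

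All SAEs go to the monitoring committee, and significant safety concerns from that committee stop the trial at the pilot stage. The article names commissioners and policy makers as its main audience. They would set any patency benefit against these counts, and without a formal test they would read the raw numbers directly.

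**Working it through.** The plan has no figure on this point to reproduce. The check is a reading of the definitions, followed by an illustration on assumed rates.

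**1. Routes into the SAE count**

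| Route | Needs a serious consequence? | Needs attribution to the anaesthetic? |
|---|---|---|
| General criteria | Yes | No |
| First trial-specific item | No | Yes |
| Second trial-specific item (re-exploration or abandonment) | No | No |

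Only the first trial-specific item depends on attribution. The second shows that a trial-specific item can be written without reference to cause.

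**2. One deficit traced through the rules.** Take a persistent deficit that is not disabling, needs no admission and is not re-explored.
- Attributed to the anaesthetic, in either group: an SAE under the first trial-specific item.
- Attributed to the dissection, in either group: an AE only.

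The class therefore depends on the attribution alone. The article does not say who makes it. That it is usually the unblinded perioperative team is an assumption, though a natural one for perioperative complications.

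**3. What later steps can repair.** SAE reports carry nature, severity and relationship to the intervention. Events that are SAEs only by the trial-specific rule can therefore largely be split off afterwards. Causality is assessed once an event is already an SAE, so neither that assessment nor the split brings back a deficit that never entered the SAE class.

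**4. Illustration of size.** Inputs: n = 283 per group (Sample size section); true persistent-deficit rate q, equal in both groups (assumed); share of deficits attributed to the anaesthetic, a_RA and a_LA (assumed).

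Expected SAEs from deficits: n × q × a_RA under regional anaesthesia and n × q × a_LA under local anaesthesia.
Difference: n × q × (a_RA − a_LA).

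With a_RA = 1:

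| q | RA count | LA, a_LA = 1 | LA, a_LA = 0.5 | LA, a_LA = 0 |
|---|---|---|---|---|
| 1% | 283 × 0.01 = 2.8 | 2.8 | 1.4 | 0 |
| 3% | 283 × 0.03 = 8.5 | 8.5 | 4.2 | 0 |
| 5% | 283 × 0.05 = 14.2 | 14.2 | 7.1 | 0 |

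The difference is zero when the shares are equal, grows as they diverge, and changes sign if a_LA exceeds a_RA.

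**The case against.** The strongest case on the other side has four parts.

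- **The rule names both techniques.** A neuropraxia attributed to local infiltration is an SAE. A deficit attributed to surgery is still an AE in the table by group, and an SAE if it is disabling, needs admission or leads to re-exploration. This stands, and it rules out saying that the deficit is counted in one group only. It does not remove the dependence on an attribution that knowledge of the allocation can influence.
- **Real block complications belong in the table.** Pneumothorax occurring mainly with a block is a true safety difference, and raising chosen events to SAE status is a cautious choice. This also stands: a genuine block complication is not an overcount.
- **The count is descriptive.** No test is run, and the monitoring committee receives event details, not just a total. This limits the harm, but details of SAEs do not supply deficits that were left outside the SAE class.
- **Table layout and form content usually sit outside a journal article.** This is fair for the split of SAEs by route, which alone would be reporting detail. The wording of the SAE item, however, is fixed in the article. No outcome listed there counts nerve deficits whatever their cause, although it says that recognised safety outcomes for nerve blocks will be recorded.

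A reader might also infer that temporary phrenic nerve paralysis swells the count in the regional group. The article mentions it only in the description of the block, where it says that "an axillary nerve block eliminates the risk of pneumothorax or temporary phrenic nerve paralysis". It is not among the listed SAE examples, and whether the open-ended list covers it is a matter of interpretation. Of the listed examples, inadvertent arterial puncture is the clear case of an event that may be trivial.

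**Conclusion.** The point holds in a limited form. The SAE count by group adds events chosen for their seriousness to events chosen for their attributed cause, and the likely attributors are unblinded. It is therefore open to differential classification, chiefly of nerve deficits that could come from either the anaesthetic or the dissection.

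The tempting stronger claim is that the table will overcount regional and undercount local anaesthesia. The documents do not support it. They give no complication rates and no attribution shares, and equal attribution gives no imbalance from this source. The illustrative gaps at half attribution in the local group are 1.4, 4.2 and 7.1 events for assumed deficit rates of 1%, 3% and 5%. They show the scale that is possible under those assumptions and are not a forecast.

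**What to change.** Keep the current SAE reporting, including that of persistent neuropraxia, and add two things.

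1. A safety item that ignores cause: any new sensory or motor deficit in the operated limb still present at the 3-month visit. It would be recorded in both groups whatever the suspected cause, by the blinded follow-up staff, and reported by group.
2. A flag on each SAE showing whether it meets the general seriousness criteria or qualifies only by the trial-specific rule, with the two sets tabulated separately by group.

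The cost is one eCRF question at an existing visit, one flag and a line of table wording. The small downside is that deficits of surgical origin are counted in both groups, which slightly dilutes any signal specific to the block. The retained SAE reporting still shows events attributed to the block.

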### Trial management and audit

The TSC, including a patient representative, will provide overall supervision of the trial and ensure that trial conduct is in line with standards set out in the EU Good Clinical Practice (GCP) Guideline.^28^ The TSC (including the chief investigator, trial statistician and five independent experts) will meet on six occasions during the trial, review blinded safety data biannually and report formally to the sponsor.

An IDMC will be responsible for monitoring data emerging from the trial, in particular, as they relate to the safety of participants. The IDMC will be completely independent of the trial and any institutions involved in the trial. It will consist of an expert clinical trialist (chair), and expert in the field of vascular access and an expert statistician. The IDMC will meet annually during the recruitment and follow-up phases of the trial. The IDMC is the only body that will have access to the unblinded comparative data during the trial. Ultimate responsibility in deciding whether or not to act on recommendations from the IDMC or a decision for early termination lies with the TSC in conjunction with the sponsor and funder.

Following risk assessment, it has been determined that the study will not be routinely monitored by the sponsor; however, the sponsor randomly selects a number of studies to be audited annually. In addition, audits can be requested by individual participating sites/TSC.

### Public and patient involvement

Patients and the public have been integral to the design and implementation of this trial. Consultation and focus groups identified both the importance of access functionality, which is reflected in our choice of unassisted functional patency as the primary outcome measure, and the ‘exhaustion and loss of control’ experienced by patients on dialysis. The trial protocol reflects these challenges such that follow-up will, where possible, be performed while the patient is on dialysis to minimise the burden additional unnecessary hospital visits, and cannulation diaries have been developed so that patients participating in the study will have some ownership for collecting data and reporting outcomes. The embedded process evaluation study will also explore patient and carer experiences of trial participation. A patient representative will sit on the TSC to ensure that the patient’s voice is heard throughout the trial. Study participants will receive results via their dialysis units, social media, renal charities and patient groups.

### Ethics and dissemination

The trial protocol has been approved by the West of Scotland Research and Ethics Committee (REC) 3 (20/WS/0178). Research will be conducted in accordance with the Declaration of Helsinki, the Principles of GCP, the Data Protection Act (2018), the General Data Protection Regulation and the UK Policy Framework for Health and Social Care Research. Substantial amendments that require review by REC will not be implemented until the REC grants a favourable opinion for the trial (amendments may also need to be reviewed and approved by the NHS R&D departments before they can be implemented in practice at local sites).

### Consent

A member of the research team will obtain written informed consent prior to administration of any trial intervention (online supplemental appendix 2). Participants will also be asked to provide consent for future data-linkage studies via the Scottish Renal Registry and UKRR. All patients will have the right to refuse participation and withdraw from the trial at any time without providing reasons and without prejudicing further treatment.

10.1136/bmjopen-2021-052188.supp2Supplementary data

### Access to data

The anonymised participant-level dataset and statistical code of generating the results will be made publicly available within 12 months of the end of trial via an online data repository.

### Ancillary and post-trial care

The anaesthetic (both regional and local) reflects a single-event intervention; therefore, contingency plans for the provision of ongoing treatment for individual trial participants is not required. The sponsor is a member of the Clinical Negligence and Other Risks Indemnity Scheme, which covers the sponsors legal liability in relation to clinical trials including clinical negligence and harm from study design.

### Publication/dissemination

Ownership of the data arising from this study resides with the grant holders. Research findings will be published in the name of the ACCess Collaborative Group, acknowledging the writing group as authors. Results of this trial will have implications for patients and clinicians across a range of disciplines including nephrology, anaesthesia, vascular access surgery and dialysis nursing. The principal target audience, however, is healthcare commissioners and policy makers. Results will be published in open-access peer-reviewed journals within 12 months of completion of the trial. We will also present our findings key national/international renal meetings and support dissemination of trial outcomes directly to patients via patient groups, renal charities and social media.
